#### Secondary outcome measure

Secondary outcome measures include the EASI [11], POEM [12, 13], DLQI [14] and VAS [15].

Secondary outcome measures are designed to be measured at Visit 1, and Visit 13.

Human-derived faeces and urine will be collected to determine changes in the gut microbiome before and after treatment. These will be sent to a specializedanalytical laboratory [16].

The timeline for the efficacy evaluation is shown in Fig. 2.

#### EASI

The EASI is used to evaluate the severity of the AD symptoms. Similar to the SCORAD index, EASI is a useful evaluation tool [11]. The body is divided into four parts (head and neck, trunk, upper limb, and lower limb) to evaluate the extent of AD lesions. The severity of symptoms (erythema, edema, papules, excoriation, and lichenification) is then evaluated.

#### POEM

The POEM is a simple, easily understood, and well-validated tool for evaluating the severity of AD symptoms in the preceding week. It is known to be appropriate for use in outpatient clinic or clinical trial settings [12, 13].

#### DLQI

The DLQI is a well-validated clinical research tool that is widely used to assess the quality of life (QoL) of patients with dermatological symptoms. It evaluates the effect of skin disease on the QoL during the preceding week and consists of 10 questions [14].

#### Pruritus VAS

The pruritus VAS will be used to assess the severity of pruritus and the degree of reduction in symptoms with treatment. The VAS consists of a 100 mm scale on which participants indicate their level of pruritus by drawing a diagonal line [15].

### Safety evaluation

Several safety measures will be undertaken, including the observation of vital signs, blood test results, drug combination, physical examination, AEs, and severe AEs outcomes. The timeline for the safety evaluation is presented in Fig. 2. If an AE occurs, researchers must quickly attend to it and record the date of occurrence, severity, duration, and treatment measures. In the case of a serious AE, the researchers must take immediate action to ensure the safety of the participants, report it to the principal investigators and the Ethics Committee within 24 h, and determine if the participant should be withdrawn based on the condition.

#### Blood Tests

Blood tests will be conducted at the screening visit and visit 13 to evaluate the general health status of the participants. The examination items will include the aspartate transaminase, alanine transaminase, alanine transaminase, γ-glutamyl transpeptidase, blood urea nitrogen, and creatinine levels. Abnormal values will be reexamined at the discretion of the investigator.

### Economic evaluation

The author will also conduct an economic evaluation alongside clinical trial to evaluate the cost effectiveness of the study treatment. The utility derived from both treatment groups will be estimated in terms of Quality-Adjusted Life Years (QALYs) using EQ-5D-5 L measurement and the national tariff equation developed in South Korea [17].

### Data management and quality control

To protect the anonymity and privacy of participants, participants’ names or identifying information will remain anonymous. The data management of this trial is based on an electronic data management system, and the data administrator constructs eCRF, whose content is derived from the “case report form”. When all the subjects complete the study, all the case report forms are entered into the system. After they are reviewed by the inspectors and checked by the data administrator, the data are locked by the data administrator.

### Statistical analysis

Professional statisticians have developed a statistical analysis plan upon consultation with the primary investigators.

#### General principles

The safety and full analysis sets (FAS) of this trial will include all the participants who received any intervention at least once after randomization. The per-protocol set will only include participants in the FAS who completed the entire trial without protocol violations. The FAS is primarily used for outcome analysis, although additional outcome analyses of the per-protocol set may be performed. The safety set will be used for safety assessments, including the primary outcome of the trial. Missing values will be handled using the last observation carried-forward method.

Statistical analyses will be performed using SAS (SAS Institute Inc., Cary, NC, USA) or SPSS (IBM Corp., Armonk, NY, USA) softwares for Windows. Statistical significance is set at *p* < 0.025 for a one-tailed test and *p* < 0.05 for a two-tailed test.

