### Randomization and allocation

As this was a multicenter trial, stratified block randomization, with the institution as a stratification factor, will be used to randomly allocate the participants to the experimental and control groups. Randomization will be performed using the SAS 9.4 statistical software (SAS Institute Inc., Cary, NC, USA). A statistician will generate randomization codes, assign serial numbers to all 184 participants, and randomly allocate them to the two groups in a 1:1 ratio to ensure reproducibility. The codes assigned to the participants through randomization will be stored in a double-locked cabinet.

If a participant is deemed eligible after the screening procedure, the investigators will open an opaque allocation envelope containing a piece of paper labeled “experimental group” or “control group” in front of the participant. The investigators will subsequently inform the participants of the allocation results and assigned intervention. Envelopes will be stored separately.

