### Blinding

Participants and outcome assessors will be blinded to the treatment group allocations. It is not possible to blind the physician; therefore, the Korean medicine doctor (KMD) who will perform the treatment will not participate in the trial outcome assessment or data collection and analysis.

Each hospital will designate several KMD trained to perform the therapy and obtain relevant operational qualifications.

The outcomes will be assessed before and after the intervention. To ensure blinding, we will choose a sham device as a placebo control in this participant-assessor-blinded clinical trial and use eye masks to shield the participants’ eyes.

The treatment device will be of the same size and material, and the treatment method will maintain a consistent frequency and intensity.

In case of serious AEs, the principal investigators at each participating center will decide whether allocation concealment needs to be broken. If allocation concealment is broken before the end of the trial, the data will be censored from the analysis and the patients will be considered to have dropped out of the trial.

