#### Economic outcomes analysis

The QALYs will be calculated using the Area Under the Curve (AUC) method. Treatment costs will be estimated by combining the frequency of each treatment and their unit costs. The economic evaluation will primarily follow the Intention-to-Treat (ITT) principle, which includes all randomized participants, regardless of adherence to the treatment protocol, to assess the effectiveness of the treatments. A secondary analysis will be performed based on the Per-Protocol (PP) principle to evaluate the sensitivity of results to missing data. For missing data in the ITT analysis, the missing data mechanism will be primarily examined using missing diagnosis method, and appropriate imputation method will be applied for building up ITT data before proceeding the analysis. The analysis period will be 8 weeks (the total follow-up period). If additional extrapolation is required, regression models or decision analysis models will be used to estimate costs and effects beyond the follow-up period. After the clinical trial period, the total analysis duration will use the 2024 South Korean currency (KRW) for cost calculations, and a 5% discount rate will be applied, in accordance with the Health Insurance Review and Assessment Service (HIRA) guidelines for cost-effectiveness evaluations. The analysis will be conducted from a societal perspective. In the base-case analysis, representative values (such as mean values) for parameters will be used, while probabilistic sensitivity analysis will be performed using all possible distributions and representative values for the estimated parameters. The results will be presented in tables, including Incremental Cost-Effectiveness Ratios (ICER), Cost-Effectiveness Planes (CEP), Cost-Effectiveness Acceptability Curves (CEAC), and Information Curve values. Statistical analysis for the economic evaluation will be conducted using Stata (MP 16.1) and R (4.3.2), and modeling for extrapolation will be performed using TreeAge Pro(Healthcare version 2023).

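### The primary analysis set leaves out randomised participants who never start treatment, and the article's allocation procedure does not ensure that starting is independent of arm

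*Protocol article*

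**What the plan says.** General principles, under Statistical analysis, gives the safety set and the FAS one shared definition: each "will include all the participants who received any intervention at least once after randomization". It then states "The FAS is primarily used for outcome analysis". The per-protocol set is a subset of the FAS, and missing values are filled by last observation carried forward (LOCF).

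Randomization and allocation sets the order of events. The step begins "If a participant is deemed eligible after the screening procedure"; at that point "the investigators will open an opaque allocation envelope containing a piece of paper labeled “experimental group” or “control group” in front of the participant". It continues: "The investigators will subsequently inform the participants of the allocation results and assigned intervention".

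Blinding says the opposite about participants: "Participants and outcome assessors will be blinded to the treatment group allocations". Of the person giving the treatment it says "It is not possible to blind the physician".

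Economic outcomes analysis uses another population. Its main analysis follows intention to treat (ITT), "which includes all randomized participants, regardless of adherence to the treatment protocol".

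**The concern.** A set that requires at least one treatment is a common and accepted departure from analysing everyone randomised. Its justification is that whether a person starts cannot be influenced by the arm. If that holds, the people lost are a similar selection from each arm and the comparison stays fair.

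The article does not establish that condition. Read literally, a participant learns the arm when the envelope is opened. Someone who hears that they are in the control group, with 12 sessions over 4 weeks ahead, may decline the first one and then drop out of the primary analysis. The unblinded physician is a second possible route, because that person can influence whether a first treatment is given. In either case the exclusion happens after randomisation and may be related to arm, so the primary comparison is no longer protected by randomisation alone.

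A second, smaller matter is that the clinical and economic results would rest on different sets of people whenever anyone fails to start, and no stated clinical analysis covers everyone randomised.

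**Working it through.** **Inputs from the article**
- Planned size: 64 per group inflated for 30% dropout (Sample size). Check: 64 / (1 − 0.30) = 91.4, rounded up to 92 per group, 184 in total. The stated figure is reproduced.
- Planning difference: 9.2 − 7.2 = 2.0 O-SCORAD points, with SDs 3.73 and 3.91 (Sample size). Pooled SD = √[(3.73² + 3.91²)/2] = 3.82. These come from a comparison with intradermal acupuncture, not with sham.

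**Inputs assumed**
- The article gives no rate of never starting. The 30% is dropout at follow-up and cannot serve as that rate. I take k = 2, 5 or 9 of 92 in one arm (about 2%, 5% and 10%) and none in the other.
- The gap between the mean change that never-starters would have shown and the mean change of the rest of their arm is taken as 3 to 5 points, in either direction.

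**Shift caused by the exclusion**

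Mean of the whole arm minus mean of those who started = (k/92) × gap.

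| k never starting | FAS | Gap | Shift (points) | Share of 2.0 |
|---|---|---|---|---|
| 2 | 92 v 90 | 3 | 2/92 × 3 = 0.07 | 3% |
| 5 | 92 v 87 | 5 | 5/92 × 5 = 0.27 | 14% |
| 9 | 92 v 83 | 5 | 9/92 × 5 = 0.49 | 24% |

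With smaller assumed gaps of 2 to 4 points and rates of 2% to 10%, the range is 0.02 × 2 = 0.04 to 0.10 × 4 = 0.40 points.

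**Scale against sampling error**

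Standard error of the difference at 92 per arm = 3.82 × √(2/92) = 0.56. The shifts of 0.07 and 0.27 are at most half of this (0.27/0.56 = 0.48). The largest, 0.49, is 0.87 of it.

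**Would widening the set be enough?**
- With LOCF retained, a never-starter's baseline value is carried to Visit 13, which is about zero change. If the rest of the arm improves by 7.2 (the comparator mean in Sample size, used here as an assumption for sham), nine such participants move the arm mean by 9/92 × 7.2 = 0.70 points. That exceeds the 0.49 it is meant to cure.
- With imputation from arm and baseline alone, never-starters receive values like those of participants who stayed. Any gap not explained by baseline remains, so the estimate is close to the treated-only one.

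Changing the set therefore helps only with a change in missing-data handling and, where possible, observed outcomes.

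**Populations side by side**
- Clinical outcomes, main: randomised and treated at least once.
- Clinical outcomes, additional: per-protocol, a subset of the above.
- Economic, main: all 184 randomised.
- Economic, secondary: per-protocol.

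**The case against.** The strongest reply is that the fault lies in the allocation procedure, not in the FAS. Blinding says plainly that participants do not know their arm, and provides a sham device and eye masks; the Fig. 3 legend describes packaging that cannot be told apart. The same section also censors data when allocation concealment is broken early, which sits badly with telling everyone. If the disclosure sentence is a drafting error, participant-driven exclusion largely disappears. This stands as a reason for caution, but the two sections do conflict, and the unblinded physician remains a possible route either way.

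The interval between disclosure and first treatment is also inferred. The exclusion criteria mention a randomisation visit, the schedule figure is not shown, and the visit numbering suggests that baseline and first treatment may share Visit 1. If so, the window for leaving is one appointment. That stands too, and it limits the likely number.

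Three stronger readings are tempting and are not supported:
- A reader might infer that the exclusions are informative as written. The documents show only that they can be. They give neither a rate nor a direction of bias.
- A reader might infer that participants will in fact be unblinded. The article says both things, so what it shows is a contradiction.
- A reader might infer that the cost-effectiveness ratio mixes populations. It does not: its effect measure is QALYs from the EQ-5D, analysed with costs in the same ITT set. The difference from the clinical set is an inconsistency to remove or explain, not an error in the ratio.

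**Conclusion.** The point holds in limited form. The primary set excludes randomised participants who never start, and the article does not secure the condition that makes such an exclusion harmless. Arm-dependent exclusion is possible through disclosure to participants, if the allocation section is followed as written, and through the unblinded physician.

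The possible bias is about 0.07 to 0.49 O-SCORAD points on wholly assumed inputs (2 to 9 of 92 in one arm only, gaps of 3 to 5 points). It is below one standard error throughout and would be negligible if almost everyone starts. The case for changing the plan rests on the low cost of protecting the comparison, not on a demonstrated large bias. The lack of any clinical analysis of all randomised participants, alongside an economic analysis that has one, supports the same change.

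**What to change.** 1. Define the FAS as all 184 randomised participants, analysed in their allocated arm, matching the economic ITT population. Restrict only the safety set to those treated at least once.
2. Seek the Visit 13 O-SCORAD from participants who never start. This is the only step that supplies the missing information directly.
3. For values still missing, use a baseline-adjusted model or multiple imputation in place of LOCF. Add a sensitivity analysis that lets never-starters and other missing participants depart from the missing-at-random assumption, by arm.
4. Keep the treated-at-least-once set as a sensitivity analysis.
5. Reconcile Randomization and allocation with Blinding so that participants are not told their arm.

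The sample size does not change. O-SCORAD is measured at screening and a score of 10 to 40 is required for entry, so every eligible randomised participant has a pre-treatment value. The costs are that the missing-data method changes as well as the set definition, a few participants with baseline data only will need imputation, and some effort is needed to obtain a final assessment from people who did not start.

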### Sample size

In our previous study, the mean changes in the O-SCORAD score for 4 weeks were 9.2 ± 3.73 and 7.2 ± 3.91 in the BMA-AD and IDA-AD groups, respectively. Based on these results, we will conservatively evaluate the changes for 4 weeks in the BMA and sham devices. The number of participants required for this study was calculated as follows:$${n}_{1}=\frac{{2({Z}_{\alpha/2}+{Z}_{\beta})}^{2}{\sigma}^{2}}{{\left(\mu1-{\mu}_{2}\right)}^{2}}=64$$

The required sample size was determined to be 64 cases per group (‘experimental group’ and ‘control group’).$$N=\frac{{n}_{1}}{1-r}\cong92$$

Assuming a 30% drop out rate of participants at follow-up, we calculated the sample size to be 92 cases for each group and a total of 184 participants for both groups.

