### Outcome measures

#### Primary outcome measure

An independent researcher will evaluate the outcomes. The schedules are listed in Fig. 2. The primary measurable outcome is the change in the O-SCORAD before (baseline) and after (5 weeks) treatment. O-SCORAD scores are designed to be measured at the screening phase, Visit 1, and Visit 13.

The O-SCORAD excludes subjective symptoms of itching and sleep disturbance from the total SCORAD [10]. A score of 15 to 40 is moderate and 1 to less than 15 is mild.

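### With efficacy scores scheduled only before treatment and at Visit 13, LOCF scores every earlier dropout as zero change, which conflicts with the sample-size calculation and can cost substantial power

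*Protocol article*

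**What the plan says.** All places are in the protocol article.

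- **Missing data and analysis set (General principles).** "Missing values will be handled using the last observation carried-forward method". The full analysis set (FAS) "will include all the participants who received any intervention at least once after randomization", so no post-baseline value is required. "The FAS is primarily used for outcome analysis"; a per-protocol analysis is optional.
- **Endpoint (Primary outcome measure).** "The primary measurable outcome is the change in the O-SCORAD before (baseline) and after (5 weeks) treatment".
- **Schedule for that endpoint, fixed in the same section.** "O-SCORAD scores are designed to be measured at the screening phase, Visit 1, and Visit 13".
- **Secondary outcomes.** "Secondary outcome measures are designed to be measured at Visit 1, and Visit 13".
- **Blinding.** This section also describes outcome assessment before and after the intervention only.
- **Treatment phase.** This section says that O-SCORAD and the other scales are checked during the four-week therapy period, but names no interim visit.
- **Sample size.** 64 per group are required. "Assuming a 30% drop out rate of participants at follow-up", the plan arrives at 92 per group and 184 in total.
- **Economic outcomes analysis.** After the missingness mechanism has been examined, "appropriate imputation method will be applied for building up ITT data before proceeding the analysis".

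**The concern.** There are 12 treatment sessions, so Visit 13 is the first scheduled measurement after treatment. A participant who stops before it has no on-treatment score, and the last observation is a pre-treatment one. LOCF then becomes baseline carried forward, with a change of exactly zero. The same holds for the secondary outcomes.

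The Sample size section assumes something incompatible. Dividing by 0.7 treats dropouts as lost, leaving 64 per arm with undiluted changes. The analysis rule keeps all 92 and sets the dropouts to zero. That shrinks the mean difference by the dropout fraction and adds variance, because each arm becomes a mixture of zeros and real changes. If dropout differs between the arms, the difference in dropout itself enters the treatment estimate. What is at stake is the power of the primary comparison and, under unequal dropout, its validity.

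**Working it through.** **Inputs.** From Sample size: mean change 9.2 (SD 3.73) with BMA and 7.2 (SD 3.91) with intradermal acupuncture (IDA), 64 evaluable and 92 randomised per arm, 30% dropout. From General principles: two-sided alpha 0.05. *Assumptions:* the IDA mean stands in for sham, for which the document gives no figure; all dropout falls before Visit 13; dropout is unrelated to the change a participant would have had.

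**The plan's own figure.** The power and SD behind 64 are not stated. With n = 2(1.96 + 0.842)² × SD² / 2.0², an SD of 4.0 at 80% power gives 62.8, so 63; a t-based calculation gives 63.8, so 64. Then 64 / 0.7 = 91.4, so 92. The figure reproduces, on the premise that dropouts leave the analysis.

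**Power as intended.** Pooled SD = √((3.73² + 3.91²)/2) = 3.82. With 64 completers per arm, z = 2.0 / (3.82 × √(2/64)) = 2.96 and power is 84%.

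**Power under LOCF with zero change.** For dropout share d, each arm has mean (1−d)μ and variance (1−d)SD² + d(1−d)μ². At d = 0.3:

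- Means: 0.7 × 9.2 = 6.44 and 0.7 × 7.2 = 5.04, so the difference is 1.40.
- BMA variance: 0.7 × 13.91 + 0.21 × 84.64 = 27.51 (SD 5.25).
- Comparator variance: 0.7 × 15.29 + 0.21 × 51.84 = 21.59 (SD 4.65).
- SE = √((27.51 + 21.59)/92) = 0.731; z = 1.40 / 0.731 = 1.92; power 48%.

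Simulation agrees: 47.8% for the t-test and 43% for the Mann–Whitney test. Restoring 80% power under this rule would take about 197 per arm.

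| Equal dropout before Visit 13 | Difference | Power, 92 per arm |
|---|---|---|
| 10% | 1.8 | 79% |
| 15% | 1.7 | 71% |
| 20% | 1.6 | 63% |
| 30% | 1.4 | 48% |

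**Sensitivity to the sham mean (30% equal dropout).**

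| Sham change | Power, difference kept at 2.0 | Power, BMA kept at 9.2 |
|---|---|---|
| 7.2 | 48% | 48% |
| 6.2 | 54% | 84% |
| 5 | 61% | 99% |
| 3 | 72% | above 99% |
| 0 | 83% | above 99% |

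**Unequal dropout, no device effect** (SD 3.82 in both arms, the same mean change in both, BMA vs sham dropout; two-sided rejection rate):

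| Common mean change | 30% vs 30% | 27.5% vs 32.5% | 25% vs 35% |
|---|---|---|---|
| 5.0 | 5.0% | 7.2% | 13.9% |
| 7.2 | 5.0% | 8.3% | 18.7% |
| 8.2 | 5.0% | 8.7% | 20.5% |

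**Unequal dropout, true difference 2.0.** With 35% dropout on BMA and 25% on sham, the LOCF difference is 0.65 × 9.2 − 0.75 × 7.2 = 0.58, the SE is 0.733 and power is 12%.

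**The case against.** Four points count on the other side.

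1. **The 48% is conditional.** The 7.2 comes from an active comparator, and the plan calls its use conservative. If sham patients improve less and BMA still reaches 9.2, the true difference exceeds 2.0; at a sham change of 6.2 or less, power is 84% or more even with the zeros. This stands. A reader might infer that the trial has 48% power, but the document does not fix the sham response, so it does not support that as a single figure.
2. **Some dropout may come after Visit 13.** The sample-size text speaks of dropout at follow-up, the Fig. 1 caption mentions week 8, and the economic analysis runs for 8 weeks. Loss after Visit 13 does not touch the primary endpoint. This also stands: if only half of the 30% leave before Visit 13, power is 71%.
3. **False positives are not established.** A reader might infer that, because unsatisfactory effect is a listed reason for discontinuation, more sham patients will leave and a useless device will look effective. With no device effect and blinded participants, lack of effect gives no reason for unequal dropout, and equal dropout leaves the type I error at 5%. Inequality would need another cause, which the document does not show. The unequal-dropout figures are what-ifs.
4. **The schedule is not wholly clear.** The Treatment phase section can be read as promising interim scores, and Fig. 2 is not reproduced in the text at hand. Interim or early-termination scores would break the exact-zero result. However, the outcome sections name the visits, and anyone leaving before a first interim score would still be scored zero.

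A reader might also take the economic section as already planning multiple imputation. It promises only an appropriate method, without naming one.

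**Conclusion.** The concern holds in conditional form. On the stated visit schedule, LOCF on the FAS means zero change for anyone who leaves before Visit 13, and this is incompatible with how the trial was sized. With the earlier study's figures, IDA standing in for sham and equal dropout before Visit 13, power falls from the intended 84% to between 79% (10% dropout) and 48% (30% dropout). The loss is smaller if sham patients improve less at the same difference, and it is outweighed if the true difference is clearly larger than 2.0. Type I error is safe under equal dropout. It would rise to about 7–9% with a 5-point gap and 14–20% with a 10-point gap towards more sham dropout, whatever the cause. A gap in the other direction would mask a real effect. Because LOCF is an explicit choice for the primary comparison, it should be changed before the data are unblinded.

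**What to change.** - **Primary rule.** For the efficacy outcomes, replace LOCF with a baseline-adjusted likelihood model, or with multiple imputation by arm using baseline score, institution and recorded rescue use. Leave out discontinuation reason: on this schedule everyone who discontinues before Visit 13 lacks the outcome, so the data cannot estimate its relation to the outcome.
- **Sensitivity analyses.** Keep baseline carried forward, and add a delta-adjusted tipping-point analysis. Both are needed because the primary method assumes that dropouts resemble completers with the same covariates, which is doubtful for people who leave because of unsatisfactory effect.
- **Schedule.** Reconcile the Treatment phase section with the Primary and Secondary outcome measure sections, and state whether any O-SCORAD is taken between Visit 1 and Visit 13 or at early termination.
- **Sample size.** State how dropouts enter the analysis, so that the 30% inflation and the missing-data rule rest on the same premise.

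The cost is revised wording and a little more programming, with no added patients or measurements. The downside is an untestable missing-at-random assumption, which the sensitivity analyses address.
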